## Description of protocol

### Study design

This single-blind randomized controlled trial will be conducted at the Rehabilitation Research Center located at the School of Rehabilitation Sciences, Ahvaz Jundishapur University of Medical Sciences, Ahvaz, Iran.

This study consists of two sessions. The first session consists of three parts; (1) pre-intervention assessments, baseline measurements will be performed by completing the questionnaires then implementing the pre-test, (2) 15-20 minutes of 24 unexpected perturbations while standing, and (3) post-test assessments. For the patients, this session will be followed by the second session 24 hours later, which include the retention and transfer tests. An overview of the study timeline, enrollment, and time points of assessment is presented in (Table 1).

**Table 1 tbl0001:** Participant flow of enrolment, assessments and interventions.

	T0	T1	TT	T2	T3
Recruitment	+				
Interview (inclusion/exclusion)	+				
Assigning Consent form		+			
Randomization		+			
Questionnaires (MMSE; NDS; BDI-13; Mini-BEST)		+			
Assessment of reactive balance responses (balance reactions while standing in pre-test, post-test, and retention test)		+		+	+
Perturbation training intervention			+		
Transfer tests		+		+	+
Dual task test transfer (Concurrent mental arithmetic task)		+			+
Rotational mode transfer		+		+	+
Choice Stepping Reaction Time (CSRT) Test		+		+	+

T0, prior to study; T1, baseline (pre-intervention); TT, training time; T2, post-intervention test; T3, second session (one day post-intervention). Abbreviations: MMSE, Mini-Mental Scale Examination; NDS, Neuropathy Disability Score; BDI-13, Short Beck Depression Inventory; Mini-BEST, Mini Balance Evaluation Systems Test.

### Inclusion and exclusion criteria

A total sample of 60 individuals with DPN and type2 diabetes aged between 45 and 60 years suffering from peripheral neuropathy (Neuropathy Disability Score: three to five), able to walk without assistive devices, having the ability to stand independently, obtaining a score above 24 on the Mini-Mental State Examination, and able to read and write the Persian language will be included in the study.

Exclusion criteria will be foot ulcer and amputation; orthopedic problems; severe pain in the soles of the feet; symptoms of central nervous system problems such as dementia, Parkinson’s disease, multiple sclerosis, and a history of stroke; uncorrected vision problems; hearing problems; a history of vertigo; suffering from peripheral vascular and heart diseases which limit exercise, such as uncontrolled blood pressure, unstable angina, and a history of resting tachycardia or arrhythmia; participation in professional or regular exercises for at least six months before the study; taking antipsychotic and anti-anxiety drugs; and depression (Short Beck Depression Inventory˃18).

The neuropathy Disability Score is a validated scoring tool used to investigate the severity of neuropathy, particularly in the extremities [15]. It evaluates vibration sense, temperature sense, pinprick sensation, and ankle reflex for quantifying the level of neurological impairments. The score ranges from 0 to 10, which scores of three to five indicate mild neuropathy [16]. The mini-Mental State Examination is a standardized questionnaire used to assess cognitive function and screen for cognitive disorders. The test consists of 11 questions, with a maximum score of 30. A score of 23 or below generally indicates cognitive impairment [17]. The short Beck Depression Inventory is designed for rapid screening and measuring of depression in adolescents and adults. A score greater than 18 indicates moderate to severe depression [18].

Patients will be referred and recruited from those visiting the diabetic department of hospitals and clinics, with an endocrinologist's approval. The outcome assessor, who will be unaware of group assignment and training, will examine the patients for the selection criteria before enrollment. This research will be conducted in accordance with the ethical recommendations of the Declaration of Helsinki. The informed consent statement will be signed by all subjects. After randomization, participants' demographic information, medical history, and prior falls will be documented.

### Random allocation

The stratified permuted block randomization method will be used to assign participants to one of the three groups: blocked PBBT, random PBBT, and the control group. It combines stratified randomization, which divides participants into two subgroups based on gender, with permuted block randomization, which uses blocks of treatment assignments to maintain balance within those subgroups. A random order of three letters, A (intervention with a random sequence), B (intervention with a blocked sequence), and C (control), will be made. The sequences will be put inside an opaque envelope.

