### Statistics

All data will be analyzed using SPSS version 28. Baseline data and demographic characteristics will be described using descriptive statistics.

Data distribution normality will be confirmed using the Kolmogorov–Smirnov test. The main effects and interactions of group (blocked sequence, random sequence, and control), time (pre-test and post-test), and difficulty level (low, medium and high) on CoP variables will be compared using three-way repeated measures ANOVA. In addition, the main effects and interactions of groups, time (post-test and retention), and difficulty level (low, medium, and high) on CoP variables will be compared using three-way repeated measures ANOVA. Also, a one-Way ANOVA will be used to compare the means of CoP variables between the retention and transfer phases across three groups. Moreover, a two-way repeated measure ANOVA will be used to determine the main effects and interactions of group and time (pre-test, post-test, and transfer) on RT, MVT, and TRT variables of the CSRT test. A post-hoc Bonferroni test will be used for multiple comparisons.

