### Sample size calculation

Due to a lack of similar studies, we conducted a pilot study on 30 individuals with diabetic neuropathy (10 for each group). Sample size was calculated in G*power software version 1.9.4.3 and was based on the primary outcome of the pilot study, the difference between means of the peak CoP velocity in the anterior direction measured with the computerized dynamic posturography at T1 and T2. Based on the statistical power of 80% and the probability of the first type error of 0.05, the sample size was estimated to be about 20 individuals in each group.

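### Randomisation is stratified by gender but no planned ANOVA contains gender, so the between-subject group tests are conservative if gender is prognostic; the group × time tests are barely touched

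*Protocol article*

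**What the plan says.** The Random allocation section of the protocol article describes "stratified randomization, which divides participants into two subgroups based on gender". Gender is the only stratification factor. Inside each of the two strata, the article plans "permuted block randomization, which uses blocks of treatment assignments to maintain balance within those subgroups".

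The Statistics section then sets out the models one by one:

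- Acquisition, CoP variables: "The main effects and interactions of group (blocked sequence, random sequence, and control), time (pre-test and post-test", plus difficulty level, "compared using three-way repeated measures ANOVA".
- Retention, CoP variables: "the main effects and interactions of groups, time (post-test and retention), and difficulty level", by the same method.
- Retention and transfer, CoP variables: "a one-Way ANOVA will be used to compare the means of CoP variables between the retention and transfer phases across three groups".
- CSRT variables: "a two-way repeated measure ANOVA will be used to determine the main effects and interactions of group and time".

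Bonferroni post-hoc comparisons follow. Gender is neither a factor nor a covariate in any of these, and nothing says how the stratification enters the analysis. The Sample size calculation section sizes the trial on the T1 to T2 difference in peak anterior CoP velocity, at about 20 per group.

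**The concern.** Blocking within gender gives the three groups nearly the same gender mix, so gender differences largely drop out of the comparison between groups. A model without gender does not know this. It leaves the variance between men and women in the error term, and the standard error of the group comparison is then larger than the design warrants. The test rejects a true null less often than 5%, and some of the precision that stratification could deliver is not used.

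At stake is efficiency in a trial of 60 people. It matters most for comparisons of outcome levels between groups. Transfer, which is one of the stated aims, is assigned to the one-way ANOVA.

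**Working it through.** **Inputs.** From the documents: 60 participants, three groups of about 20, two gender strata, two-sided or one-sided testing not stated, and "Based on the statistical power of 80% and the probability of the first type error of 0.05". Not given: the effect size, the SD, the test used for the sample size, and R², the share of within-group variance of the analysed quantity that gender explains. R² is therefore an assumed range.

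**The plan's own figure.** The 20 per group cannot be reproduced forward, because no effect size or SD is stated. Solving backwards for a three-group one-way F test with N = 60, 80% power and alpha 0.05 gives f = 0.411. That value is used as the true effect below.

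**Between-subject tests: simulation.** 60 participants, exact 1:1:1 allocation within each gender, equal numbers of men and women, 20,000 runs per case; F test for group without gender (2 and 57 df) and with gender (2 and 56 df).

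| Assumed R² | Type I error, without gender | Type I error, with gender | Power, without | Power, with |
|---|---|---|---|---|
| 0 | 0.047 | 0.048 | 80% | 80% |
| 0.02 | 0.048 | 0.051 | 80% | 81% |
| 0.05 | 0.043 | 0.050 | 80% | 82% |
| 0.10 | 0.036 | 0.050 | 80% | 84% |
| 0.20 | 0.025 | 0.051 | 81% | 88% |

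The simulation error of a type I rate near 0.05 is √(0.05 × 0.95 / 20,000) = 0.0015, so the 0.047 at R² = 0 is compatible with 0.05. A 30:70 gender split gives nearly the same results.

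**Check by formula.** With exact balance, the group mean square has expectation (1 − R²) under the null, while the error mean square averages (1 − R²) + (60/57)R². The F test therefore acts as if its critical value of 3.159 were multiplied by k = [(1 − R²) + (60/57)R²] / (1 − R²). With 2 numerator df, P(F > x) = (1 + 2x/57)^(−28.5).

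- R² = 0.05: k = 1.055, x = 3.334, P = 0.043.
- R² = 0.10: k = 1.117, x = 3.528, P = 0.036.
- R² = 0.20: k = 1.263, x = 3.990, P = 0.024.

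These agree with the simulation.

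**Group × time tests.** With two time points, the group × time test is an ANOVA on the change score, averaged over difficulty. A gender effect that is the same at both times subtracts out. Simulated without gender in the model, with correlation 0.5 between time points:

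| Gender effect (SD) | Gender × time effect (SD) | Type I error, group × time | Type I error, group main effect |
|---|---|---|---|
| 0.5 | 0 | 0.051 | 0.036 |
| 1.0 | 0 | 0.050 | 0.018 |
| 1.0 | 0.3 | 0.047 | 0.012 |
| 1.0 | 0.5 | 0.044 | 0.011 |

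The reason the interaction test moves so little can be seen directly. At correlation 0.5 the variance of the change is 2 × (1 − 0.5) = 1. A gender × time effect of 0.3 or 0.5 SD adds 0.3²/4 = 0.0225 or 0.5²/4 = 0.0625, so gender's share of the variance of the change is only 0.0225/1.0225 = 0.022 or 0.0625/1.0625 = 0.059.

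**The case against.** Much of the case on the other side stands.

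- **Scope.** A reader might infer that every planned model is conservative because every one omits gender. The documents do not support that. Three of the four planned analyses are repeated-measures ANOVAs, and acquisition and retention are read from group × time, as is the sample size from the T1 to T2 difference. A stable gender effect cancels there.
- **Condition.** Nothing in the documents says that gender predicts CoP or CSRT outcomes. If it does not, there is no loss. Choosing gender as the only stratification factor suggests that it was thought to matter, but that is not a figure.
- **Size.** A reader might also infer that the trial is underpowered. It is not, on this account: power without gender stays at 80% to 81% over R² from 0 to 0.20. What is given up is a gain of about 2 points at R² = 0.05 and 4 at 0.10.
- **Ambiguity.** The sentence on the one-way ANOVA can be read as comparing group levels at retention and transfer, or as comparing the difference between phases. On the second reading a stable gender effect cancels there too.
- **Condensed source.** The article is short, and a full protocol or SAP may add gender. That objection is weaker. The Statistics section does not leave the model terms open: it lists them for each analysis, and the factor used to randomise is not among them.

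**Conclusion.** The mismatch between allocation and analysis is in the text. Its consequence is limited to the tests that compare levels between groups: group main effects, the retention and transfer one-way ANOVA so far as it compares levels, and Bonferroni comparisons of group means. For these, an assumed R² of 0.05 to 0.20 means a true type I error of about 0.043 down to 0.025 and a forgone power gain of 2 to 7 points (80% against 82%, up to 81% against 88%). At R² = 0 there is no effect. For group × time tests the effect is nil when the gender difference is stable, and small in the cases simulated where it is not.

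The sizes rest on the assumed R², on exact balance within gender (incomplete blocks would loosen it a little), and on an effect back-solved from 20 per group. The direction is always conservative: no estimate is biased and no type I error is inflated. This is a worthwhile improvement in efficiency of low to moderate weight, and does not make any planned result invalid.

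**What to change.** Prespecify gender as a between-subject factor, without a group × gender term, in each model in the Statistics section. In the repeated-measures models, let gender interact with time, and with difficulty where that is a factor. A gender main effect alone would leave the error term of the group × time test as it is; the interaction terms are what adjust the within-subject error terms.

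The cost is one between-subject degree of freedom (57 to 56 error df in the one-way case) and the matching within-subject degrees of freedom. If gender turns out not to matter, power is about 80% either way. The Protocol validation section says that the outcome assessment phase has not been reached, so the change can still be made before outcome data exist and cannot be taken for a data-driven choice.

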### Interventions

For the intervention groups (random and blocked PBBT), the training will be performed by a different physical therapist. Patients in the control group will receive no intervention.

Participants will be stand on two force platforms of computerized dynamic posturography with one foot on each of the platforms. The intervention involves restoring body balance after unexpected perturbations through movement of the support base in the anteroposterior direction, for both directions at three levels of difficulty. Participants will be verbally instructed to maintain their body balance after support base displacements. Ground reaction forces underneath each leg will be recorded by two adjacently placed movable platforms of the computerized dynamic posturography device.

Participants will wear a safety harness supported by ropes tied at shoulder height, with the other end attached above their head. While these ropes will not limit balance recovery movements, they prevent participants from falling.

Researchers selected three difficulty levels for reactive balance training: low difficulty (3cm displacement amplitude; 5cm/s peak velocity and 70cm/s^2^ peak acceleration), medium difficulty (7/5cm displacement amplitude; 10cm/s peak velocity and 137cm/s^2^ peak acceleration), and high difficulty (15cm displacement amplitude; 15cm/s peak velocity and 260cm /s^2^ peak acceleration). From combining perturbation directions (anterior and posterior) and three difficulty levels of platform motion, six conditions of block perturbations will be generated.

In each block, participants will perform four trials for each perturbation condition, given by the combination of direction and difficulty levels, totaling 24 trials. In the blocked group, each balance perturbation will be repeated over blocks of four trials for participants. For the random group, the four perturbations of each block will be scheduled pseudorandomly and unpredictably, with no repetition of a perturbation condition (difficulty × direction) in consecutive trials.

The intervention groups will perform this single session PBBT after a five-minute rest at the end of the examining pre-intervention tests. The duration of each trial is 10 seconds and a 10 second rest is allowed between trials. In addition, a one-minute rest is given between blocks.

### Methods of measurement

Participants will be evaluated at a pre-test (T1), post-test (T2), and retention test (T3) using the same protocol. In these tests, each participant will receive two trials of perturbations with each of the three difficulty levels and the anterior direction with a serial sequence (totaling six trials). Serial sequence refers to the sequence or arrangement of different skills, or variations of a skill, in a specific order, one after another in a predictable manner. The post-test is applied five minutes after PBBT.

The retention test will be applied at the beginning of the second session. After a five-minute rest, patients will be tested in three different transfer tasks.

Transfer tasks will be assessed as follows:

Cognitive dual-tasking: counting backward by three from a random number selected between 100 and 200 by the outcome assessor during perturbations. Participants will be asked to maintain balance while they attempt to perform the consecutive mental subtractions task as quickly and as accurately as possible, speaking aloud the result. During this cognitive transfer task, the high level of difficulty perturbation will be applied in the anterior direction, with two trials.

Different mode of perturbation: In this test, the perturbation will be in the anterior (dorsiflexion) direction with a rotational mode, with two trials.

Choice Stepping Reaction Time (CSRT) Test: for assessing the transferability of improvements obtained in the reactive balance responses to the balance responses against internal perturbations, the CSRT test will be used. In this test, patients will stand on a long force plate of the Neurocom device with their feet hip-width apart, and while looking at the screen in front of them, colored boxes are randomly displayed on the right or left side of the screen. Participants will be instructed to step as fast as possible with the respective leg and then return to the starting position. Each participant will perform 10 trials, which include five repetitions for each direction randomly [19]. A one-minute rest period will be allowed between transfer tests. In order to have a baseline in this study, all transfer tests will be assessed before training.

Reactive balance control is the main outcome in this study, which will be recorded with the Computerized Dynamic Posturography system in the standing position [20].

Reactive response variables will be collected by the Smart EquiTest CRS (NeuroCom International Inc.Clockamas, Oregon) device, including: (1) peak center of pressure (CoP) displacement in anterior and posterior directions which indicates the maximum distance that the location of the CoP reaches in the anterior or posterior direction relative to the baseline [21]; (2) response time, defined as the time interval between the start of platform movement (as a stimulus) and the initiation of the participant's active response; (3) peak values of CoP velocity in the anterior and posterior directions following the onset of platform motion.

CSRT test is used to measure how quickly and accurately a person can step in response to a visual stimulus [22]. The equipment will be used consisted of the long single force plate (EquiTest CRSVR NeuroComVR International, Clackamas, OR) and the screen in front of patients.

In the step execution data, the following temporal variables will be examined: (1) Reaction time (RT) defined as the time interval between the appearance of the stimulus and the movement initiation (lifting the corresponding leg); (2) Movement time (MVT) defined as the time interval between the start of the movement and the foot strike; and (3) Total response time (TRT) calculated as the sum of RT and MVT [23].

In addition to other interventions, the Mini-Balance Evaluation Systems Test (Mini-BESTest) will be performed as a clinical assessment tool. This test evaluates dynamic balance, particularly in individuals with balance impairments [24].

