Using the practice schedule concept of motor learning to PBBT is a relatively new approach [8]. There are two types of practice schedules:constant and variable. Constant practice involves repeatedly practicing a single skill. In contrast, variable practice exposes the learner to a variety of related skills [9]. Performing variable skills within a single practice session creates contextual interference (CI), a phenomenon that enhances long-term learning by requiring frequent shifts between task variations [10]. Variable practice is broadly categorized into blocked or random schedules [11]. Blocked practice, associated with low CI, involves repeated performing of one task before moving to another, facilitating skill acquisition and performance during training [11]. Random practice, associated with high CI, refers to practice task variations in the same session in a pseudo-random order [11]. Although acquisition may be slower, random practice leads to better skill retention and transfer to new situations [12].

Given the crucial role of reactive responses in preventing falls, which are often sudden and occur in any direction [13], it is important to investigate how different practice schedules affect the ability of individuals with DPN to react to balance perturbations. In addition, In individuals with DPN, compensating for sensory loss increases cognitive demand, causing balance impairments during dual-tasking [6]. Since reactive balance requires attention, dual tasks may further disrupt postural control strategies in these individuals [14]. Therefore, assessing the generalizability of improvements in reactive balance control during single-task to dual-tasks may be useful for enhancing dual-task interference on reactive balance performance in individuals with DPN.

To the best of our knowledge, no study has yet investigated the effects of different practice schedules of PBBT on reactive balance control in individuals with DPN. Therefore, this study aims to compare the effects of blocked and random practice of PBBT on the acquisition, retention, and generalizability of acquired reactive balance skills in individuals with DPN. Our findings would be helpful for the development of preventive and therapeutic strategies to reduce the risk of falls and improve reactive balance control in individuals with DPN.

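### The dual-task and rotational CoP tests have a T1 baseline that no stated analysis uses, and the only CoP transfer comparison either cannot show transfer or gives up precision

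*Protocol article*

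**What the plan says.** The Background states the aim as to "compare the effects of blocked and random practice of PBBT on the acquisition, retention, and generalizability of acquired reactive balance skills". Methods of measurement names three transfer tests: a cognitive dual task during high-difficulty perturbations, a rotational perturbation, and the CSRT test. It places them in the second session, after the retention test: "After a five-minute rest, patients will be tested in three different transfer tasks". It also explains why they are run before training: "In order to have a baseline in this study, all transfer tests will be assessed before training". Table 1 (Study design) agrees. It marks the dual task at T1 and T3, and the row "Rotational mode transfer" at T1, T2 and T3.

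Statistics specifies four analyses. Two three-way ANOVAs on CoP variables cover pre-test to post-test and post-test to retention, by difficulty level; neither includes a transfer test. The third is the only one that names transfer for CoP: "a one-Way ANOVA will be used to compare the means of CoP variables between the retention and transfer phases across three groups". The fourth concerns CSRT only: a "two-way repeated measure ANOVA will be used to determine the main effects and interactions of group and time (pre-test, post-test, and transfer" phases as its levels of time.

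**The concern.** The protocol gives a reason for measuring the transfer tests at baseline, follows it through for CSRT, and then drops the baseline for the two tests that carry CoP variables. Those variables measure reactive balance control, which Methods of measurement calls the main outcome, and the Background argues specifically for dual-task transfer.

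The contrast written for these two tests also raises a question of meaning. Retention and transfer are both measured at T3, in the same patients, on different tasks. A difference between them says how much harder one task is than the other, plus any shortfall in transfer. At stake is whether the CoP part of the generalizability aim gets an answer that can be read as transfer, and whether that answer uses the precision the design pays for.

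**Working it through.** **1. Inputs.** From the protocol: three groups, about 20 per group, type I error 0.05, and a control group without training. Not in the protocol: effect size, SD, and the correlation between measurements. Assumed here for illustration: SD 1, a gain of 0.8 SD in both trained arms, and a common correlation ρ of 0.3 to 0.7 among the measurements. Gains are scored so that improvement is positive.

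**2. The plan's own figure.** About 20 per group at 80% power cannot be reproduced, because Sample size calculation gives no effect size, SD or test. Solving backwards, n = 20 implies a standardised difference of about 0.89 for two arms (normal approximation), or f of about 0.41 for a three-group one-way ANOVA. The figure rests on peak anterior CoP velocity from T1 to T2, so it does not speak to transfer.

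**3. Reading A: a retention-minus-transfer contrast.** Let c be the fixed difference between the two tasks, g_r a group's gain on the retained task, and g_t its gain on the transfer task. The expected gap at T3 is

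gap = c + (g_r − g_t).

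- Control, no training: c + (0 − 0) = c.
- Trained, full transfer: c + (0.8 − 0.8) = c.
- Trained, no transfer: c + (0.8 − 0) = c + 0.8.

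The first two are equal for any gain, SD or correlation. The gap moves only when transfer is incomplete or exceeds the trained gain.

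Rejection rates follow from the noncentral F. With group means 0.8, 0.8 and 0, the grand mean is 0.533 and f² = (2 × 0.267² + 0.533²)/3 = 0.142. With variance 1 the noncentrality is 60 × 0.142 = 8.53. The gap has variance 2(1 − ρ), so with no transfer the noncentrality is 8.53/[2(1 − ρ)].

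| True state | Gap test rejects |
|---|---|
| No training effect | about 5% |
| Full transfer, 0.8 SD in both trained arms | about 5% |
| Full transfer, random gains 1.0 and blocked 0.5 | about 5% |
| No transfer, ρ = 0.3 / 0.5 / 0.6 / 0.7 | about 57% / 72% / 82% / 92% |

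Simulation with 10,000 runs per setting agrees. The third row matters most for the aim: the two schedules truly differ on the transfer task, and the contrast does not see it.

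Two further faults belong to this reading. First, c is not a nuisance that cancels by design. Retention spans three translational levels, the dual task uses only the high level plus arithmetic, and the rotational test is another mode. Second, a one-way ANOVA with phase as the factor treats paired values as independent: it takes the variance of a within-patient difference as 2 when it is 2(1 − ρ), for example 0.8 at ρ = 0.6.

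**4. Reading B: a one-way ANOVA by group at the transfer phase.** Under full transfer the noncentrality is 8.53 on 2 and 57 degrees of freedom, which gives power of about 72%. ANCOVA on the T1 value reduces the residual variance to 1 − ρ², so the noncentrality becomes 8.53/(1 − ρ²) on 2 and 56 degrees of freedom. A change-score (group × time) analysis has 8.53/[2(1 − ρ)] on 2 and 57.

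| ρ | T3 only | Change T3 − T1 | ANCOVA noncentrality | ANCOVA power |
|---|---|---|---|---|
| 0.3 | 72% | 57% | 9.38 | 77% |
| 0.5 | 72% | 72% | 11.4 | 84% |
| 0.6 | 72% | 82% | 13.3 | 90% |
| 0.7 | 72% | 92% | 16.7 | 95% |

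These are overall three-group tests with equal gains in both trained arms, so they measure trained against control. For random minus blocked the picture is thinner. With illustrative gains of 1.0 and 0.6 at ρ = 0.6, the standard error is √(0.64 × 2/20) = 0.253, the ratio is 0.4/0.253 = 1.58, and ANCOVA power is about 34%.

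**The case against.** Four points can be made for the plan.

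- A reader might infer that the generalizability aim goes untested. The protocol does not support that. CSRT is one of the three transfer tests, its times are listed among the primary outcomes, and its analysis includes the pre-test. This point stands, and the concern is limited to the dual-task and rotational CoP values.
- A reader might also infer that the CoP transfer comparison is invalid in every case. It is not. A one-way ANOVA has a single factor, the sentence mentions three groups, and no difference score is defined. If group is the factor at the transfer phase, the T3 comparison is a proper randomised one. This stands too: on that reading only precision is lost. The phrase about comparing means between two phases still leans toward the contrast, and the protocol does not settle it.
- The gap would not be read alone, because the pre/post and post/retention ANOVAs show whether the trained arms learned and kept the skill. That helps interpretation. It does not turn the gap into a test of transfer, since a non-significant gap is not evidence of full transfer.
- The size of the power gain depends on a correlation that the protocol does not give. Each CoP transfer test has only two trials, so a low correlation is possible, and at 0.3 the gain is only about five percentage points. This is why a range is shown.

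**Conclusion.** The concern holds for the two CoP transfer tests and not for CSRT. Two parts need no assumed numbers: no stated analysis uses the T1 dual-task or rotational CoP values, and a retention-minus-transfer contrast has the same expectation under full transfer as under no training. Which fault applies depends on how the sentence is read. As a contrast, it does not test transfer. As a group comparison at T3, it is valid but has about 72% power where ANCOVA would have about 77% to 95%. Those power figures assume a 0.8 SD gain in both trained arms, 20 per arm and correlations from 0.3 to 0.7, and they do not describe the power for random against blocked. The same edit improves the plan on either reading. It should be made before analysis, but it does not put the whole trial in doubt.

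**What to change.** Replace the one-way ANOVA sentence in Statistics. For each CoP transfer test (dual-task, rotational mode), use ANCOVA with the T3 value as outcome, the same test's T1 value as covariate and group as factor. Report random minus blocked, and each trained arm minus control, with confidence intervals. Keep the retention-to-transfer gap as description only. The T2 rotational measurement marked in Table 1 can be analysed the same way as a secondary time point.

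A group × time model like the one for CSRT would also bring in the baseline. ANCOVA is the safer choice here, because with T1 and T3 alone the group × time test has less power than ignoring the baseline when the correlation is below 0.5 (57% against 72% at 0.3).

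The cost is one sentence and one residual degree of freedom (57 to 56). No visit or measurement is added, since Table 1 already schedules T1 and T3 for both tests. Protocol validation says the outcome assessment phase has not been reached, so the change can be recorded before any results are seen.
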